**Figure 3 fig3:**
[figure not shown]
Position and orientation of the segment coordinate system of upper limbs and trunk. Blue axis is for flexion (Z), green is the rotation axis for upper-limb and adduction axis for hand (X), and red is the adduction axis for upper-limb and the axis rotation for hand (Y). In grey the frontal plan from landmarks. Adapted from Maillet et al. (47).

**Figure 4 fig4:**
[figure not shown]
Representation of the placement of kinematics markers.

### Data analysis and management

#### Sample size

The sample size will be reach based on the availability of the OBGY residents and surgeons in our department and their availability during work hours. We estimate the sample size to reach 30 participants. Previous literature had shown similar sample sizes various between 5 and 20 (34, 35, 45). Such sample size (30 participants) base on time resource constraint (50), according to GPower 3.1 software calculation, allows detecting a moderate effect size of *f* = 0.30 with a power of 0.8 for the Wilcoxon signed-rank test with a level of significance of 5%.

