**Methods and analysis:**

A controlled cross-over laboratory trial involving 29 residents and surgeons from the obstetrics and gynecology department of Nantes University Hospital is underway. Recruitment started in March 2023 and ended in September 2023. Participants with varying levels of experience perform two one-hour sessions of training box exercises, one in the morning (control condition) and the other at the end of a workday. The primary outcome is a composite score derived from the time to complete the Suturing and Knot Tying Training and Testing (SUTT) exercise, along with the number and quality of stitches. Secondary outcomes include perceived fatigue, discomfort, physical strain, muscle tension, mental workload, muscle activation (measured by surface electromyography), balance (measured using a force platform), and kinematics (measured using motion capture).

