#### Statistical analysis

The level of significance for all statistical analyses will be set at 0.05 under the bilateral hypothesis.

Our primary outcome represented by the time to complete the SUTT task will be analyzed using the Wilcoxon signed-rank test.

The normality of quantitative data will be assessed using a graphical method and a Shapiro test. The dimensional consistency of the subjective data will be calculated using Cronbach’s alpha coefficient. We employed a Type III ANOVA to analyze the EMG data, assessing the significant effects of both experimental sessions (i.e., control versus fatigue) while accounting for potential variations between muscles, thereby ensuring a robust evaluation of the factors influencing muscle activation patterns.

To study our secondary outcomes with the force platform, we will conduct a multivariate analysis of variance (ANOVA) as a protected procedure to test the statistical dependence of the COP excursions, maximum COP velocities.

In EMG’s we will conduct an ANOVA to test the statistical dependance of RMS and MPF.

In kinematics, to compare CMC and range of between the two sessions, a one-way ANOVA with post-hoc (Bonferroni) will be performed for each DoF.

All statistical tests will be performed using Jamovi version 2.3.28.

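### The stated 80% power pairs an ANOVA effect size (f = 0.30) with a Wilcoxon signed-rank test and cannot be reproduced from the inputs given

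*Protocol article*

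**What the plan says.** The Sample size section explains that the number of participants was set by staff availability and time: "We estimate the sample size to reach 30 participants". It then reports a G*Power 3.1 calculation, according to which this number "allows detecting a moderate effect size of *f* = 0.30 with a power of 0.8 for the Wilcoxon signed-rank test" at a 5% significance level.

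The Statistical analysis section fixes the remaining inputs. The primary outcome "will be analyzed using the Wilcoxon signed-rank test", and sidedness is set for the whole trial: "The level of significance for all statistical analyses will be set at 0.05 under the bilateral hypothesis". Under Study design each participant acts as his or her own control, so the sample size is a number of pairs.

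The article gives no mean difference, standard deviation, within-person correlation or assumed distribution of the differences, and does not say how f was carried over to a paired test. The abstract describes the trial as enrolled: "A controlled cross-over laboratory trial involving 29 residents and surgeons".

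**The concern.** The test, number of pairs, significance level, sidedness and claimed power are all printed, so the claim can be checked. The effect size does not belong with the test. A signed-rank calculation takes dz, the mean paired difference divided by the standard deviation of the differences. Cohen's f is an analysis-of-variance measure, and turning it into dz requires the correlation between a participant's two sessions.

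Because availability fixed the sample size, this sentence is the article's only statement of what the trial can detect. If the primary comparison is null, a reader may use it to judge which effects can be ruled out. Someone who takes 0.30 as the paired effect would believe the trial had an 80% chance of finding it, when on that reading the chance is about one in three.

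**Working it through.** **Inputs.** From the article: n = 30 pairs, effect 0.30, power 0.80, alpha 0.05, two-sided, Wilcoxon signed-rank test. Assumed, because the article does not say: the distribution of the paired differences and, where needed, the within-person correlation ρ.

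**Method.** Noncentral t with n multiplied by the asymptotic relative efficiency (ARE) of the signed-rank test: 3/π = 0.955 for normal differences, 0.864 as the theoretical minimum, π²/9 = 1.097 for logistic, 1.5 for Laplace. With m = n × ARE, the degrees of freedom are m − 1 and the noncentrality is dz × √m.

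**Attempt to reproduce 80%, with 0.30 read as dz.** For normal differences, m = 30 × 0.955 = 28.65, df = 27.65, critical t = 2.050 and noncentrality = 0.30 × √28.65 = 1.606. Two-sided power is 0.341.

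| Distribution of differences | Two-sided power | One-sided power | n for 80% (two-sided) | Detectable dz, n = 30 |
|---|---|---|---|---|
| Normal | 0.341 | 0.469 | 94 | 0.543 |
| Minimum ARE | 0.312 | 0.437 | 104 | 0.573 |
| Logistic | 0.386 | 0.516 | 82 | 0.504 |
| Laplace | 0.503 | 0.632 | 60 | 0.427 |

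A paired t-test gives 0.355 and a plain normal approximation 0.376. No variant reaches 0.80. Simulation of the signed-rank test (20,000 runs, normal differences, n = 30, two-sided) gives 0.344 at dz = 0.30 and 0.802 at dz = 0.54, which supports the approximation. For Laplace differences it gives 0.469 at dz = 0.30, so the tabulated 0.503 is slightly generous. With 29 pairs and normal differences, power is 0.331 and the detectable dz is 0.553.

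**0.30 read as Cohen's f.** With two conditions d = 2f = 0.60, and dz = d / √(2(1 − ρ)). At n = 30, normal differences, two-sided:

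| ρ | dz | Power |
|---|---|---|
| 0 | 0.424 | 0.59 |
| 0.3 | 0.507 | 0.75 |
| 0.5 | 0.600 | 0.87 |
| 0.7 | 0.775 | 0.98 |

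The correlation that gives exactly 80% comes from setting dz to the detectable value: ρ = 1 − 0.36 / (2 × dz²). For normal differences, 1 − 0.36 / (2 × 0.543²) = 0.39. The same formula gives 0.29 for logistic (dz 0.504), about 0.01 for Laplace (0.427) and 0.45 at the minimum ARE (0.573).

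A repeated-measures ANOVA at f = 0.30, the setting in which f would be natural, behaves alike: power 0.61 at ρ = 0, 0.80 at 0.35 and 0.89 at 0.5.

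**0.30 read as d on the raw standard deviation.** Under normality, 80% two-sided needs ρ of about 0.85: dz = 0.548, power 0.807.

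**The case against.** The strongest defence is that the printed symbol is f, not dz. Taken literally it means d = 0.60, and 30 participants then give 80% or more at any within-person correlation of about 0.39 or higher under normality, and at lower correlations if the differences have heavier tails. This stands as far as it goes. The 34%, the 94 participants and the one-in-three chance all depend on reading 0.30 as dz, which the article does not say. A reader might infer that the trial is underpowered, or that 80% is false on any reading; the document supports neither. The defence does not rescue the sentence, though, because it needs a correlation that is not stated and a conversion that is not shown.

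A reader might also see an error in 30 planned against 29 enrolled. It is not one: a planning calculation properly uses the planned number, and the difference barely matters (0.34 against 0.33 at dz = 0.30).

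It is also true that power did not drive the sample size and that recruitment has closed, so no design choice hangs on the figure. That limits the consequence to how the results are read, but the published claim still needs correcting.

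**Conclusion.** The power statement is wrong as written: its effect-size measure does not match its test, and its 80% does not follow from its stated inputs. The true figure depends on what 0.30 was meant to be. At 30 pairs, two-sided 5% and normal differences, power is about 34% if it is dz and 59% to 98% if it is f with a correlation between 0 and 0.7. What can be said without guessing the intended meaning is the detectable effect: dz of about 0.54 with 30 participants and 0.55 with 29 under normality (0.43 to 0.57 across the distributions considered, at n = 30). These values rest on the efficiency-adjusted noncentral t, which simulation confirms for normal differences. No other section of the article supplies the missing correlation or conversion.

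**What to change.** Delete f = 0.30 and replace the power sentence with wording such as:

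*With 30 planned (29 recruited) participants, a two-sided Wilcoxon signed-rank test at 5% has 80% power to detect a standardised paired difference dz of about 0.54 (0.55 with 29), assuming normally distributed differences; power for dz = 0.30 is about 34% (33%).*

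The cost is one sentence, and a less favourable stated figure if 0.30 was meant as dz. No extra participants and no change to the analysis are needed. The Trial status section says that no analysis has begun, so the correction can still be made before any result is known.

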#### Data management

The recruiting clinicians will keep a register with a study number and all identifiable data (name, phone number, mail, pseudonymization code) for use. The “data will be stored in a locked cabinet in the department of gynecology accessible only by the main investigator ([name]). The digital data will be saved on an external hard drive. Data will be stored for a period of 10 years after the publication of the results.

#### Statistical analysis

The level of significance for all statistical analyses will be set at 0.05 under the bilateral hypothesis.

Our primary outcome represented by the time to complete the SUTT task will be analyzed using the Wilcoxon signed-rank test.

The normality of quantitative data will be assessed using a graphical method and a Shapiro test. The dimensional consistency of the subjective data will be calculated using Cronbach’s alpha coefficient. We employed a Type III ANOVA to analyze the EMG data, assessing the significant effects of both experimental sessions (i.e., control versus fatigue) while accounting for potential variations between muscles, thereby ensuring a robust evaluation of the factors influencing muscle activation patterns.

To study our secondary outcomes with the force platform, we will conduct a multivariate analysis of variance (ANOVA) as a protected procedure to test the statistical dependence of the COP excursions, maximum COP velocities.

In EMG’s we will conduct an ANOVA to test the statistical dependance of RMS and MPF.

In kinematics, to compare CMC and range of between the two sessions, a one-way ANOVA with post-hoc (Bonferroni) will be performed for each DoF.

All statistical tests will be performed using Jamovi version 2.3.28.

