### Experimental procedures

Our experiment will consist in simulated laparoscopy tasks conducted in a Pelvic Trainer (Szabo, ID Trust Medical, Belgium). The control and fatigue sessions will begin by filling out questionnaires (Fatigue sensation scale, physical strain, and motivation). Before starting the simulated experimental task, participants will be equipped with sEMG electrodes and kinematics markers.

We will use an optic in the Pelvic trainer, including a camera and a light source (Optic 0°, Karl Storz). The optic will be connected to a screen in front of the participants (TELE PACK, Karl Storz). The Pelvic trainer will be disposed on a manually adjustable table to adapt the height to each participant according to their preference. Participants will be placed on a force platform (PFA6040M35 Sensix) at the beginning of each set, in a position that will perfectly replicate the one used during standard laparoscopic simulation.

The experimental session will be a series of three different tasks. The Laparoscopic Skills Training and Testing (LASTT) exercises (hand-eye coordination that we will call “LASTT,” and bimanual coordination that we will call “LASTTbis”) will be performed with a 3-min time limit. A 15-min time limit will be set for the Suturing and Knot Tying Training and Testing (SUTT) exercises (see Supplementary material 2 for a detailed description and a graphic representation of each exercise). The Pelvic trainer exercises will be performed on the side of the table to reproduce the conditions of pelvic surgery, a setup that has been underexplored. All tasks will be conducted under the supervision of an experimenter ([name]). EMG, force platform and kinematic data (see below) will be recorded during the experimental session. The timeline of a session is presented in Figure 2.

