### Outcome measurements

Table 1 provides a summary of the measures that will be collected and that will serve for analysis in this study.

**Table 1 tab1:** Summary of measures to be collected.

Outcome	Instrument	Time of measurement	Unit
Primary outcome			
Performance	Composite score of time to complete the task associated with quality assessment	SUTT task	0–900
Secondary outcomes			
Muscle activation	RMS static 10th percentile muscle activity	SUTT task	(%MVE)
	RMS Median 50th percentile muscle activity	SUTT task	(%MVE)
	RMS Peak 90th percentile muscle activity	SUTT task	(%MVE)
Muscular fatigue	MPF: Mean power frequency	SUTT task	Hz
Force platform	M/L COP excursion	LASTT, LASTTbis and SUTT task	Cm
	A/P COP excursion	LASTT, LASTTbis and SUTT task	Cm
	M/L COP velocity	LASTT, LASTTbis and SUTT task	Cm/s
	A/P COP velocity	LASTT, LASTTbis and SUTT task	Cm/s
Kinematics	Range of Motion in the 18 DoF		Degree (°)
	Coefficient of multiple correlation (CMC)	SUTT TASK	
Perceived workload	NASA-TLX (English)	Total of 6 items	0–120
	SURG-TLX (English)	Total of 6 items	0–120
Motivation	VAS	Pre-Task and post task	(0–10)
Physical strain	Borg CR-10 Scale: legs, back, neck, Right and left shoulders and right and left arms	Pre and post task	(0–10)
Physical fatigue	VAS	Pre and post test	(0–10)
Effort	VAS	Post test	(0–10)

A/P, Antero posterior; COP, Center of pressure; DoF, Degrees of freedom; M/L, Mediolateral; LASTT, Laparoscopic Skills Training and Testing; MPF, Median power frequency; MVE, maximal voluntary electrical activity; NASA-TLX, National Aeronautics and Space Administration Task Load Index; RMS, Root mean square; SUTT, Suturing and Knot Tying Training and Testing; VAS, Visual analogic scale.

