#### Primary outcome: performance during a surgical simulated task

Our primary outcome will be the performance and will be assessed by the amount of time and numbers and quality of the stitches done during the SUTT exercise. We expect a decrease in performance during the “fatigue” session.

The time to complete the task will be assessed (in seconds) for every LASTT, LASTTbis and SUTT exercises combined by a quality assessment of the task (numbers of stiches completed withing 15 min, quality of stiches and nod). Every stich must be done by entering and existing within the black dots. The number of threads passes through each point (between 0 and 10, one pass per point through each black dot). A correct stitch equal one point on a 0–5 scale (5 being the total number of stiches). A correct Knot is rated 2 points if completed correctly and solid. Absence of trauma on the dot is rated on a 0 to 2 scale. All quality scales and the time to complete the task will be added to a online scoring platform called +he Academy’s Online Scoring Platform to produce a composite score going to 0–900.

For data analysis, we will keep only the best time to complete the task among the 3 trials for LASTT and LASTTbis.

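### The primary outcome is defined as a 0–900 composite of SUTT time, stitch number and quality, but the only primary test is on completion time alone

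*Protocol article*

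**What the plan says.** Three places in the protocol article define the primary outcome as time combined with quality.

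- Abstract, Methods and analysis: "The primary outcome is a composite score derived from the time to complete the Suturing and Knot Tying Training and Testing (SUTT) exercise", together with stitch number and quality.
- Table 1 under Outcome measurements: "Composite score of time to complete the task associated with quality assessment", for the SUTT task, with range 0–900.
- Primary outcome section: performance is "assessed by the amount of time and numbers and quality of the stitches done during the SUTT exercise". The quality part covers "numbers of stiches completed withing 15 min, quality of stiches and nod". The ratings and the time are entered in an online platform "to produce a composite score going to 0–900".

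The Statistical analysis section reads differently: "Our primary outcome represented by the time to complete the SUTT task will be analyzed using the Wilcoxon signed-rank test". No other sentence assigns a test to the primary outcome, and no analysis of the composite is described.

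Experimental procedures adds a limit: "A 15-min time limit will be set for the Suturing and Knot Tying Training and Testing (SUTT) exercises".

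**The concern.** The variable that is defined and the variable that is tested are not the same, and they can disagree in two ways.

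First, time says nothing about how well the stitches were placed, whether the knot held, or whether the target was damaged. The introduction itself raises the possibility that surgeons adapt to fatigue at some cost in movement quality. A participant who hurries when tired and sutures worse would improve on time, while the composite was built to register the loss.

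Second, time is bounded by the 15-min limit, and counting the stitches finished within that limit implies that some sessions may end incomplete. Among sessions stopped at the limit, time alone cannot separate a session with four stitches from one with two.

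At stake is the trial's main conclusion: whether a workday reduces performance would be judged on a variable other than the one announced as primary.

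**Working it through.** **1. The definitions side by side**

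| Place | Primary variable | Quality included? |
|---|---|---|
| Abstract, Methods and analysis | Composite score | Yes |
| Table 1 | Composite score, 0–900 | Yes |
| Primary outcome section | Time plus number and quality of stitches, scored 0–900 | Yes |
| Statistical analysis | SUTT completion time | No |

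The Sample size section does not settle it. Its power statement names neither time nor the composite, and gives no difference or SD in seconds or points. The ranges do not help either: 15 min × 60 s = 900 s, so the upper end of the composite equals the time limit in seconds.

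**2. What the time test does at the limit**

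Suppose, as an assumption, that an unfinished session is recorded as 900 s. A participant stopped in both sessions then has a difference of 900 − 900 = 0, whatever was achieved in each. The usual signed-rank test discards zero differences. A participant stopped in one session only keeps a difference, but a shortened one.

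**3. How much power this could cost**

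The plan's own figure is power 0.8 with 30 participants and f = 0.30 for the signed-rank test. Read as a standardised paired difference of 0.30 at two-sided 0.05 ("The level of significance for all statistical analyses will be set at 0.05 under the bilateral hypothesis"), it does not reproduce: the power is about 0.34 under normality. Power of 0.80 with n = 30 needs a standardised paired difference of about 0.54. That is a separate matter. Here 0.54 serves only to start the illustration at the plan's 0.8.

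Input from the documents: limit 900 s, n = 30, two-sided 0.05, Wilcoxon signed-rank test.

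Assumed, not in the documents:
- normally distributed uncapped times with SD 150 s
- within-person correlation 0.5, so the SD of the paired difference is 150 × √(2 × (1 − 0.5)) = 150 s
- true slowing of 0.54 × 150 = 81 s
- unfinished sessions recorded as 900 s, and zero differences removed

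The control mean was set to 900 − 150 × z(1 − share), where share is the proportion of control sessions reaching the limit. Simulation with 4,000 runs per row gave:

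| Control sessions at the limit | Zero differences | Zero pairs of 30 | Power uncapped | Power capped | Loss |
|---|---|---|---|---|---|
| 2% | 1% | 30 × 0.01 ≈ 0 | 0.79 | 0.79 | about 0.01 |
| 25% | 18% | 30 × 0.18 ≈ 5 | 0.80 | 0.70 | 0.10 |
| 50% | 42% | 30 × 0.42 ≈ 13 | 0.80 | 0.57 | 0.24 |
| 75% | 70% | 30 × 0.70 = 21 | 0.80 | 0.32 | 0.48 |

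Losses are taken before rounding (first row 0.791 − 0.7855 = 0.0055; last row 0.80225 − 0.324 = 0.478).

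A second set of assumptions (n = 29, between-person SD 150 s, within-session SD 80 s, slowing again 0.54 SD of the paired difference) shows the same pattern. Uncapped power is about 0.77. With mean times of 650, 850 and 950 s it becomes 0.75, 0.57 and 0.40, with 5%, 33% and 57% zero differences.

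**The case against.** The strongest reply is that the Statistical analysis sentence is loose shorthand. Three places agree on the composite and one does not, and since the score's range matches the time limit in seconds, the score may be built largely on time. That is possible, but the scoring formula sits on a platform that is not shown, and the sentence does not say that it means the composite. The reply makes the intention easier to guess and leaves the sentence in need of correction. An analysis plan that is not shown does not remove the point either, because the article itself states both versions.

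The second reply is that the power argument is not drawn from the documents. This stands. They give no mean, no SD, no share of sessions reaching 15 min, and no rule for the value of an unfinished session. The loss may be negligible. The composite might also have ties or a floor when time runs out; the documents do not allow that to be checked.

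A reader might go further and infer two things that the documents do not support.

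- That power is lost chiefly among trainees, who are expected to show the largest effect. The Subgroup analysis section expects a larger impact in trainees for muscular or mental fatigue. It does not mention SUTT performance, and nothing says that trainees reach the limit more often.
- That two primary endpoints are deliberately kept open so that one can be chosen after seeing the data. The text shows an inconsistency and no such intention. It does leave the choice unfixed, which is reason enough to close it.

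**Conclusion.** The point holds as a contradiction within the article: the primary outcome is a 0–900 composite in three places, and the test assigned to it uses completion time alone. This rests on the wording and needs no assumption. It follows directly that the test as written cannot register a loss of suturing quality and would count a faster, poorer session as better.

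The effect of the 15-min limit is conditional. If unfinished sessions are recorded as 900 s, the illustrated power loss runs from about 0.01 with 2% of control sessions at the limit to about 0.48 with 75%, under the assumed means, SDs and correlation. Where the trial lies in that range cannot be told from the documents. The need for correction does not depend on it.

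**What to change.** Before analysis, replace the sentence in the Statistical analysis section with: *The primary outcome, the SUTT composite score (0–900), will be compared between the control and fatigue sessions using the Wilcoxon signed-rank test.* Report completion time only as a component of the score or as a supportive result.

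If the sponsor prefers time as the primary outcome, change the abstract, Table 1 and the primary-outcome section to match, and state what value a session stopped at 15 min receives.

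The cost is a change of wording. No new data are needed, and the Trial status section reports that analysis had not started.

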## Methods and analysis

### Study design

We will compare the fatigue outcomes during 1 h of laparoscopic box test training in the morning with the same session performed after a whole-day work. Our study will be based on a cross over model, each participant will be his own control. We will try to show if the fatigue induced by a full day of work leads to changes in surgeon’s performance, quality of movement including upper body posture, perceived workload, and surgeon’s motivation.

We will conduct a controlled cross over study, following the SPIRIT guidelines. Every participant will perform two separate experimental days: (i) the first one planned in the morning, i.e., without any work intervention before testing (control day), (ii) the second one planned at the end of a full workday (fatigue day). The experimental sessions will always be performed on different days. The order of the days will be randomized to control which participant completes the control day or fatigue day first. Each participant will be included for a period of 6 months. Approximately 6 months of recruitment will be required to reach the target sample size. 6 month is the time needing to collect participant’s information, to perform a test training session and randomized participant for the experimental days. Recruitment started in March 2023 and ended in September 2023. Data collection is planned to last until May 2024 and analysis until September 2024. The flow chart of our study is presented in Figure 1.

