##### Kinematics

For kinematics analysis, a motion capture system composed of seven cameras (Vicon Vero 2.2) will be used. We will record kinematics data for seven joints (Figure 3) with a total of 18 degrees of freedom. Three-dimensional position of the thorax, arms, forearms, hands will be considered during the movement using the kinematic model (47, 48). We will base our model on an existing model that has been used by our team in a movement analysis study performed on seamstresses (47). Twenty-nine spherical reflecting markers (4 mm in diameter) will be placed on anatomical landmark of upper limbs and thorax. Markers placements are visible in Figure 4 and details of the markers disposition are available in Supplementary material 1. For practical reasons related to the use of laparoscopic forceps and the limited fine motor skills in the fingers during laparoscopy, we will eliminate the distal markers located at the hands. Before each motion capture, we will perform a capture in a neutral posture, the arms slightly in abduction with a slight internal rotation at the shoulders (abduction <30°) (49). Ranges of motion of the different degrees of freedom and CMC will be extracted.

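### The Bonferroni step planned for kinematics acts on a two-session factor within each degree of freedom, so it adjusts nothing across up to 36 tests

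*Protocol article*

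**What the plan says.** The protocol article, Statistical analysis, sets one level for everything: "The level of significance for all statistical analyses will be set at 0.05 under the bilateral hypothesis". For the motion-capture data it adds: "In kinematics, to compare CMC and range of between the two sessions, a one-way ANOVA with post-hoc (Bonferroni) will be performed for each DoF". The word after the second measure is missing, but Table 1 and the Kinematics section show that range of motion is meant.

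Study design fixes the factor: "Every participant will perform two separate experimental days", a control day and a fatigue day, with each participant as his or her own control.

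The Kinematics section gives the number of variables: "We will record kinematics data for seven joints (Figure 3) with a total of 18 degrees of freedom", and then "Ranges of motion of the different degrees of freedom and CMC will be extracted". Table 1 under Outcome measurements lists "Range of Motion in the 18 DoF" and CMC as secondary outcomes. It ties only range of motion explicitly to the 18 DoF. That CMC is also tested per DoF rests on the Statistical analysis sentence.

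The article states no adjustment across DoF or across the two measures.

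**The concern.** A Bonferroni post-hoc adjusts the pairwise contrasts among the levels of the factor that has just been tested. Here that factor is session, with two levels, and the ANOVA is fitted separately for each DoF. There is only one contrast to adjust, so the step has no effect. The multiplicity that does exist runs across the DoF and the two measures, and the sentence does not reach it.

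This is more than a missing detail. The plan names a correction and attaches it where it cannot work, so a reader could take the kinematic results to be protected when they are not. The same section describes the force-platform analysis as a multivariate procedure meant to guard against multiple testing, which suggests the authors wanted some error control for secondary outcomes. At stake is how far reported movement changes can be trusted. The study means to use them, with other measures, to explain any fall in performance.

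**Working it through.** **Inputs from the protocol article**
- Level per test: 0.05, two-sided (Statistical analysis).
- Levels of the session factor: 2 (Study design).
- DoF: 18 (Kinematics; Table 1).
- Measures: 2, range of motion and CMC (Kinematics; Statistical analysis).

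**1. Effect of the stated correction.** Contrasts among 2 sessions = 2 × 1 / 2 = 1. Adjusted level = 0.05 / 1 = 0.05, which is the plan's unadjusted level. On simulated data, the p-value from a two-level one-way ANOVA and that of its single Bonferroni-adjusted contrast agreed.

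**2. Number of tests.** 18 × 2 = 36. If CMC is a single summary, 18 + 1 = 19. For one measure alone, 18.

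**3. Error if every test has a true size of 0.05 and all nulls hold.** Expected false positives = m × 0.05, whatever the correlation between tests. Chance of at least one under independence = 1 − 0.95^m.

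| Tests (m) | Expected false positives | At least one, if independent |
|---|---|---|
| 18 | 0.90 | 60.3% |
| 19 | 0.95 | 62% |
| 36 | 1.80 | 84.2% |

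**4. Correlated DoF.** The DoF describe linked segments during one task, so independence is doubtful. The article gives no correlations. The values below are assumptions (equal correlation among all statistics, 100,000 simulated draws).

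| Assumed correlation between tests | At least one, 18 tests | At least one, 36 tests |
|---|---|---|
| 0.3 | 51% | 71% |
| 0.5 | 40% | 55% |
| 0.7 | 28% | 36% |
| 0.9 | 15% | 18% |

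All exceed 5%, but for 36 tests the chance is below one half from 0.7 upwards.

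**5. If the one-way ANOVA is run unpaired.** The design is paired, and an unpaired test ignores the correlation between a participant's two sessions. When that correlation is positive, the test overstates the standard error of the difference and its true size falls below 0.05. Simulated with 29 participants (the number in the abstract), normal data and 200,000 draws; the correlations are again assumptions. Expected count = 36 × size; chance of at least one = 1 − (1 − size)^36, taking the 36 tests as independent.

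| Assumed within-participant correlation | True size | Expected false positives, 36 tests | At least one |
|---|---|---|---|
| 0 | 0.050 | 1.8 | 84% |
| 0.2 | 0.029 | 1.0 | 65% |
| 0.3 | 0.020 | 0.7 | 52% |
| 0.5 | 0.007 | 0.25 | 22% |
| 0.7 | 0.0008 | 0.03 | 3% |

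**6. After a correction across the right family.** Bonferroni over 36 tests: 0.05 / 36 = 0.00139 per test, with family-wise error 1 − (1 − 0.00139)^36 = 4.9% if independent. Over 18 tests within one measure: 0.05 / 18 = 0.00278 per test, again 4.9% for that measure. Two families each held at 5% allow up to 1 − 0.95² = 9.75% across both if independent.

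**The case against.** The best reply is that the authors meant Bonferroni across the DoF and worded it loosely, with the family spelled out in a fuller plan not shown here. That is possible. The printed sentence, however, makes the step a post-hoc of an ANOVA run separately per DoF. Even on the generous reading it does not say whether the family is 18 or 36, so it still needs rewriting.

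A second reply is that secondary outcomes need no formal error control, and the article nowhere promises it across them. That stands as a general position and limits the weight of the point. It does not rescue a named correction that does nothing.

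A third reply concerns size, and much of it stands. The 1.8 expected false positives need tests of exact size 0.05, and the 84% also needs independence. The article writes one-way ANOVA without calling it repeated-measures. Taken literally, the test may reject too seldom, and lost power may then matter more than false positives.

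A reader might infer three stronger things that the document does not support:
- **That a false kinematic finding is likely.** This depends on correlations, and on a choice of test, that the article does not settle.
- **That the study's account of mechanism rests on these tests.** EMG, the force platform and the questionnaires also inform it.
- **That the results will be published as corrected when they are not.** This predicts conduct; the article shows only that the planned step, as worded, would allow it.

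**Conclusion.** The point holds in a limited form. As written, the Bonferroni step has a multiplier of 1 and gives no protection across the 18 DoF and two measures. That conclusion needs no assumption beyond the wording and the two-session design.

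Its numerical consequence is conditional on how the ANOVA is run. With a paired or repeated-measures analysis of true size 0.05, the counts in steps 3 and 4 apply, and every scenario examined leaves the family-wise error well above 5%. With an unpaired analysis and positive within-participant correlation, the false-positive figures shrink, at the price of sensitivity. The primary Wilcoxon signed-rank test is untouched. This should be corrected, but it concerns one secondary domain among several.

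**What to change.** Delete the post-hoc step and replace the sentence with wording such as: *For each DoF, range of motion and CMC will be compared between sessions with a paired (repeated-measures) analysis; p-values will be adjusted by Holm-Bonferroni across all kinematic tests (18 DoF × 2 measures).* If CMC is a single summary, state the family as 19.

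Two alternatives are acceptable if stated in advance. One is two families of 18, with a note that error is then controlled per measure only. The other is Benjamini-Hochberg, with the kinematic results labelled exploratory.

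The change takes one sentence. The Trial status section says analysis has not begun, so it can be made before any result is known. The cost is that fewer kinematic results will be called significant: under Holm over 36 tests, the smallest p-value must reach 0.05 / 36 = 0.00139.
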